### Blood Sampling and Analysis

In addition, 20 mL of venous whole blood will be collected in ethylenediaminetetraacetic acid, serum, RNA exact, and DNA exact tubes (Sarstedt) at 4 points in time: during premedication, immediately postoperatively, on the second postoperative day, and on the fifth postoperative day. Serum and plasma samples, proteins, DNA, and RNA will be extracted from these whole blood samples. Furthermore, specific cell fractions such as neutrophils, macrophages, and peripheral blood mononuclear cells will be isolated. Proteins will be isolated from these cell samples and, together with plasma, subjected to the proteomic analysis using mass spectrometry to identify potentially significant proteins. Concurrently, an analysis of candidate genes, such as ACHE, BCHE, CHRNA7, chemokines, and cytokines, will be conducted to investigate methylation processes associated with the occurrence of POD. For methylation analysis, DNA samples are subjected to bisulfite conversion, and methylation will be quantified using quantitative polymerase chain reaction with specific primers [17]. The activity of acetylcholinesterase and butyrylcholinesterase will be assessed using ELISA (enzyme-linked immunosorbent assay).

In addition, an in silico analysis of the identified target genes will be performed to identify potential polymorphisms. Polymorphisms that appear potentially relevant will be genotyped in the entire patient cohort using the TaqMan Assay (TaqMan SNP Genotyping Assays; Thermo Fisher) [18,19]. In the final step, the identified genes and proteins will be quantified together with known inflammatory markers (tumor necrosis factor-α, interleukin-6 [IL-6], and interleukin-10) from serum samples using ELISA or the LegendPlex assay (BioLegend) [20]. The blood plasma obtained during cell isolation will also be used for measuring tumor necrosis factor-α and other cytokines (IL-6, interleukin-10, etc) via ELISA. In addition, neuron-specific enolase and S-100 β protein levels will be determined from the remaining blood preoperatively and 48 hours and 5 days postoperatively. The remaining DNA, RNA, and plasma samples will be stored at −20 °C and −80 °C to ensure the possibility of repeat measurements in case of technical errors. The samples will also be preserved for further validation of significant proteins from the proteomic analysis using ELISA and to investigate their genetic basis (polymorphisms and DNA methylation).

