### Clinical Data Collection and Processing

A formal Data Monitoring Committee is not required for this study, as there are no interventions being tested and no anticipated risks to participants beyond standard clinical care. Therefore, no interim analyses or stopping guidelines are planned.

The study conduct will be monitored by the study physician and the research team according to standard operating procedures to ensure data quality and protocol adherence. Since there are no safety concerns beyond routine care, no additional independent monitoring is planned.

Clinical parameters are systematically documented and collected throughout the project. These parameters are exported from the routine medical documentation within the various subsystems of the electronic health records. On regular wards, this will be done through the Hospital Information System, and in ICUs, through the Patient Data Management System, capturing the entire course of patient treatment. The clinical data include vital parameters, medications, diagnoses, procedures, and laboratory values. Anesthesia documentation is supplemented by a digital Anesthesia Information Management System, which closely monitors all perioperative anesthesia parameters, including medication, vital signs, and ventilation parameters. Intraoperative electroencephalogram data, recorded during anesthesia depth monitoring, will also be captured.

These routinely collected data will be supplemented by explicitly requested variables to determine study end points, such as delirium scores. For this purpose, a study nurse will assess delirium preoperatively, upon transfer from the recovery room, and on the 5 subsequent postoperative days using the CAM, or CAM-ICU if the patient is transferred to the ICU. A learning effect from repeated testing is only to be expected in patients without delirium. Other outcome parameters include neuropsychological status measured by the Repeatable Battery for the Assessment of Neuropsychological Status, health-related quality of life assessed with the 36-item Short Form Health Survey, and mortality on the day of hospital discharge, as well as on days 30 and 90 after surgery.

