### Integrative Data Analysis and AI Model Development

This section describes the planned integration and analysis of clinical and multiomics data for the exploratory investigation of potential predictors of POD. Data will be analyzed both independently and in combination with a focus on patient groups with and without POD. Prior to analysis, clinical datasets will be preprocessed; for example, variables with more than 30% missingness will be discarded, whereas remaining gaps will be imputed, where applicable, when missing at random, using multiple imputation by chained equations or other suitable methods. Clinical continuous variables will be centered and scaled to *z* scores, and categorical variables will be one-hot encoded. In proteomics, the analysis will involve deriving accurate quantitative protein data from peptide data, particularly by improving the utilization of shared peptides found in multiple proteins.

Univariate analyses, such as *t* tests and ANOVA (with adjustments for multiple comparisons), will be applied to identify candidate features, which may subsequently be subjected to pathway and enrichment analyses to generate mechanistic hypotheses regarding molecular processes potentially involved in POD. Multivariate techniques, including principal component analysis and clustering, will be applied to uncover latent patient phenotypes beyond a priori groupings.

The significant findings from clinical and omics data are fed into a knowledge base for targeted searches, facilitating focused investigations (targeted proteomics). The entire dataset is also analyzed using multivariate methods, including principal component analysis and clustering, to reveal latent patient phenotypes beyond a priori groupings. Supervised prediction of POD will rely on a benchmark suite of algorithms (eg, regularized logistic regression, random forests, support vector machines, and gradient-boosting methods). Model training and hyperparameter tuning will follow a nested cross-validation scheme, supplemented by a temporally separated holdout set when sufficient data are available. Discrimination and calibration will be reported with area under the receiver operating characteristic curve, area under the precision-recall curve, sensitivity, specificity, accuracy, and *F*-score. The final modeling protocol will be chosen on the basis of performance, interpretability, and clinical plausibility and can be iteratively updated as additional data accumulate.

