### Strengths and Limitations

The CONFUSED study has several strengths. First, it employs a prospective observational design with standardized perioperative data collection and systematic delirium assessments using validated instruments (CAM and CAM-ICU). Second, blood samples are collected at multiple perioperative time points, enabling the investigation of dynamic molecular changes associated with the onset and progression of delirium.

Third, the study integrates multiple layers of molecular data, including proteomics, transcriptomics, DNA methylation, and genetic polymorphisms. This multiomics approach provides a comprehensive view of the biological processes involved in the delirium development. Finally, the application of ML methods for data integration and predictive modeling may improve the identification of clinically relevant biomarker signatures.

Several limitations should be considered. First, the study was conducted at a single center, which may limit the generalizability of the findings to other clinical settings or patient populations. Second, although the planned sample size is sufficient for exploratory analyses, validation in independent cohorts will be necessary to confirm the predictive performance of the identified biomarkers and models.

Third, the high dimensionality of multiomics data combined with a relatively moderate sample size may increase the risk of overfitting in predictive modeling. To address this challenge, appropriate statistical methods, cross-validation strategies, and feature selection approaches will be applied. Finally, while peripheral blood samples provide valuable information about systemic biological processes, they may not fully capture neurobiological mechanisms occurring within the central nervous system.

Other challenges should be considered. Privacy and security concerns, the need for extensive and diverse datasets, and the complexity of translating AI findings into clinical practice are notable hurdles [27-29]. While AI can identify associations and patterns, understanding the underlying mechanisms of POD and establishing causality requires further research.

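### Late-draw protein, ELISA, cell-fraction and AChE comparisons of patients with and without POD may mix delirium biology with drugs and intensive care given after onset

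*Protocol article*

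**What the plan says.** Blood Sampling and Analysis sets the draws "at 4 points in time: during premedication, immediately postoperatively, on the second postoperative day, and on the fifth postoperative day". Table 1 ticks the last blood collection on day 4 instead; the point is the same for either day. Under Clinical Data Collection and Processing, a study nurse assesses delirium before surgery, on transfer from the recovery room, and "on the 5 subsequent postoperative days using the CAM, or CAM-ICU if the patient is transferred to the ICU".

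Integrative Data Analysis and AI Model Development states: "Data will be analyzed both independently and in combination with a focus on patient groups with and without POD". It names t tests and "ANOVA (with adjustments for multiple comparisons), will be applied to identify candidate features". These features may go on to pathway and enrichment analysis to "generate mechanistic hypotheses regarding molecular processes potentially involved in POD", and significant findings go on to targeted proteomics.

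Strengths and Limitations lists the repeated draws as a strength, "enabling the investigation of dynamic molecular changes associated with the onset and progression of delirium". The limitations given there are the single center, the need for external validation, overfitting, and peripheral blood as a window on the brain, with a general remark that causality needs more research. Care given between onset and sampling is not named.

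On the data available: "The clinical data include vital parameters, medications, diagnoses, procedures, and laboratory values". ICU data come from the Patient Data Management System.

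**The concern.** A patient who becomes delirious on day 1 may have been given sedatives or antipsychotics, or moved to the ICU, before the day-2 sample is taken. The Introduction itself links POD to longer ventilation and greater care needs. Care that follows from case status is not balanced by enrolling more patients. Multiplicity adjustment does not remove it either, because that adjustment controls chance findings and not confounding.

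The late assays include cytokines and cholinesterase activity, which drugs or intensive care could plausibly alter. If a late marker reflects care rather than delirium, it can pass into pathway analysis and targeted proteomics as a candidate mechanism. Restricting a prediction model to data from before onset would not cure this, because the mechanistic comparison is a separate analysis.

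**Working it through.** **1. Can onset precede the draw?** Yes, on the article's own schedules. POD found on leaving the recovery room or on day 1 precedes the day-2 draw. POD first found up to day 3 (if the last draw is on day 4) or day 4 (if on day 5) precedes the last draw.

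**2. Which data are exposed?** Table 1 ticks RNA microarray and epigenetic analysis only at baseline and in the recovery room, and genotyping only at baseline. The text has DNA and RNA tubes filled at all four draws, but no later transcriptomic or methylation analysis is scheduled. Proteomics, ELISA and cell isolation are ticked on day 2 and at the last draw, and AChE on each of days 1 to 5. The concern is confined to these late data.

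**3. How large could it be?** The article gives no figure to reproduce: no share of patients treated and no drug effect. What follows is an illustration.

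Inputs from the article: 100 POD cases and 200 to 300 patients, hence 100 to 200 controls (Sample Size Considerations). Assumptions: the marker has no association with delirium, its SD is 1, treatment shifts it by d SD, and a share f of cases is exposed before the draw.

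- Apparent POD effect = f × d. If a share g of controls is exposed too, it becomes (f − g) × d. The figures below take g = 0, so they are upper values for each f.
- SE = √[(1 + f(1 − f)d²)/100 + 1/controls].
- Rejection probability from the normal approximation, two-sided.

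Worked case, f = 0.50 and d = 0.5: the apparent effect is 0.25 SD. With 100 controls, SE = √(0.010625 + 0.01) = 0.1436 and z = 1.74, so P(p<0.05) = 41%. With 200 controls, SE = √(0.010625 + 0.005) = 0.125 and z = 2.00, so P(p<0.05) = 52%.

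| f (d = 0.5) | apparent effect, SD | P(p<0.05) | P(p<0.001) |
|---|---|---|---|
| 0 | 0 | 5% | 0.1% |
| 0.10 | 0.05 | 6-7% | 0.2% |
| 0.25 | 0.125 | 14-17% | about 1% |
| 0.50 | 0.25 | 41-52% | 6-10% |
| 0.75 | 0.375 | 75-85% | 25-39% |

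The ranges run from 100 to 200 controls; p<0.001 stands in for multiplicity adjustment. At f = 0.50, P(p<0.05) is 18-23% for d = 0.3 and 78-87% for d = 0.8. If the case count is instead 72 of 300 (the article's 24%), d = 0.5 gives 19%, 44% and 72% at p<0.05 for f = 0.3, 0.5 and 0.7.

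**4. What would discarding exposed cases cost?** Take a true 0.5 SD marker. With all 100 cases, z = 0.5/√(1/100 + 1/100) = 3.54 or 0.5/√(1/100 + 1/200) = 4.08. Against the critical value 3.29, power at p<0.001 is about 60% or 79%. If 75% are exposed, 25 cases remain: z = 0.5/√(1/25 + 1/100) = 2.24 or 0.5/√(1/25 + 1/200) = 2.36, and power is about 15% or 18%.

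**The case against.** The article describes no delirium treatment. It mentions ICU transfer only as the reason to use CAM-ICU, which applies to any patient, and says that few effective therapeutic approaches exist. Controls aged 75 or over after medium to major surgery can also receive sedatives or ICU care. A reader might infer that treatment reaches cases only; the article does not support that, and exposure in controls shrinks the bias.

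The wording is also modest. Changes are said to be associated with onset and progression, pathway results are called hypotheses, and the study is declared exploratory, with external validation required. A reader might infer that drug effects will be reported as delirium biology, but at a 10% exposed share the distortion is negligible.

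The tests are given as examples, and Trial Status says that a separate protocol and statistical analysis plan exist. Exposure adjustment may be set out there, so its absence from a condensed article is not in itself a fault.

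All of this stands, and it limits the claim to a possible distortion of unknown size in the late-draw data. What remains is that the article presents the late draws as showing onset and progression, describes a two-group comparison that cannot by itself separate delirium from care given after onset, and does not name this among its limitations.

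**Conclusion.** The point holds in a limited form. On the stated schedules, the day-2 and last samples of some cases can follow POD onset and the care it prompts. The comparison of patients with and without POD in late proteomic, ELISA, cell-fraction and AChE data may therefore mix the two.

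It would be wrong to extend this to all the omics layers: Table 1 keeps transcriptomic and methylation analysis at baseline and the recovery room, and genotype is fixed. The preoperative clinical model uses no blood samples and is also unaffected.

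The size depends on two quantities that the article does not give: the excess share of cases exposed before the draw and the shift that exposure causes. Over the assumed ranges the distortion runs from negligible to dominant. The point merits a change because the records needed to examine it are already being collected and, by the article's account, recruitment is ongoing and final data lock has not occurred.

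**What to change.** Use the delirium assessments and the exported medication and ICU records to label every postoperative sample, in cases and controls alike, in two ways: before or after POD onset (for cases), and before or after sedative or antipsychotic exposure or ICU transfer. Fix in advance how to class a sample drawn on the day of the first positive assessment, since daily assessments may not order the two.

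Keep the full late-draw comparison. Beside it, report the comparison for pre-onset or unexposed samples and for post-onset or exposed samples. Before pathway analysis or targeted proteomics, flag late-draw markers seen only in exposed cases as possibly treatment-related. Do not exclude them: unexposed cases may be milder or later in onset, and a rule that a marker must also hold in them would discard true markers, as step 4 of the working shows. The strata are a sensitivity analysis and not a replacement.

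Add the limitation to Strengths and Limitations, and reconcile the day-4 and day-5 timing of the last draw so that the labels are well defined.

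The cost is a derivation from existing data, some analysis text, and strata that are smaller and less precise than the full comparison. No new samples or visits are needed. The labels require event times in the exported records, which the article does not state and which should be confirmed.

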### Future Directions

The findings of the CONFUSED study may provide the basis for future research aimed at validating identified biomarkers and predictive models in independent multicenter cohorts. In addition, the identified molecular pathways may represent potential targets for preventive or therapeutic interventions.

In the long term, the integration of molecular biomarkers with clinical risk factors could enable the development of personalized perioperative risk assessment tools and targeted prevention strategies for POD.
